# Efficacy and safety of using a warming needle for persistent allergic rhinitis: study protocol for a randomized controlled trial

**DOI:** 10.1186/s13063-016-1432-z

**Published:** 2016-06-30

**Keywords:** Acupuncture, Warm needling, Persistent allergic rhinitis, RCT, Study protocol

## Abstract

**Background:**

Many previous studies have shown the potential therapeutic effect of acupuncture for allergic rhinitis. Most of these studies, however, were limited by the short duration of observations and lack of sham acupuncture as the control group. Our preliminary experiments showed that the use of a warm needling achieved a much more persistent effect in the treatment of allergic rhinitis (AR) compared with simple acupuncture therapy. Hence, we have designed a multicenter, randomized controlled trial (RCT) in which the first-line medication loratadine will be used as the control group, and the effect of warm needling therapy will be evaluated through long-term observation.

**Methods/design:**

The trial is designed as a multicenter, parallel-group, randomized, single-blinded (outcome assessors), non-inferiority trial. A total of 98 patients with persistent AR will be randomly assigned into two groups. Patients in the treatment group will be treated with warm needling at GV14 and acupuncture at EX-HN3, ST2, LI20, EX-HN8, GV23, LU7, LU5 and LI4 three times a week, for a total of 4 weeks. Patients in the control group will be treated with oral loratadine 10 mg/day for 4 weeks. The primary outcome will be the change in the Total Nasal Symptom Score (TNSS) from baseline to that at 6 months after treatment during the follow-up period. The secondary outcomes will include the Total Non-nasal Symptom Score and the Rhinoconjunctivitis Quality of Life Questionnaire, changes in the TNSS from baseline to that at 2 and 4 weeks during treatment, and 3 months after treatment during the follow-up period. Outcomes will be measured at 2 and 4 weeks, and 3 and 6 months after treatment. Any side effects of treatment will be observed and recorded.

**Discussion:**

We expect that the study results will provide evidence to determine the effects of warm needling compared with loratadine. Our final goal of the study is to evaluate the difference in the short-term and long-term effects between the two therapeutic methods, especially the long-term effect of warm needling.

**Trial registration:**

ClinicalTrials.gov NCT02339714. Registered on 14 January 2015.

**Electronic supplementary material:**

The online version of this article (doi:10.1186/s13063-016-1432-z) contains supplementary material, which is available to authorized users.

## Background

Allergic rhinitis (AR) is a symptomatic nasal disorder resulting from an IgE-mediated immunological reaction to allergen exposure [1]. AR is a worldwide health problem affecting people of all ages. The reported incidence of AR is 11.8–46 % worldwide [2, 3] and 11.1–19.1 % in China [4, 5]. AR is classified into intermittent allergic rhinitis (IAR) and persistent allergic rhinitis (PAR) according to the time of exposure. The major symptoms of AR include rhinorrhea, nasal itching, nasal obstruction, and sneezing. These symptoms can resolve spontaneously or with treatment. AR may cause disruption in sleep cycles and emotional balance, and impair daily activities [6]. Untreated AR can also trigger other diseases such as bronchial asthma, sinusitis, nasal polyps, otitis media, and allergic conjunctivitis, resulting in significant psychological disturbance and economic burden [7].

The current mainstream medical management of AR primarily includes allergen avoidance, pharmacotherapy, immunotherapy and patient education. These treatments, however, do not always provide complete relief of symptoms and are not usually cost-effective, and like other medications they come with undesirable side effects [8, 9]. Although newer-generation medications have been developed, the issue of side effects has not been resolved [10]. Furthermore, pharmacotherapy only provides quick symptom relief in the case of PAR and becomes less effective in recurrent cases due to the development of medication tolerance [11]. Immunotherapy can reduce the natural duration of AR and provide symptom control; however, it can cause a local or systemic anaphylactic reaction [12]. Therefore, a safe and long-term effective treatment modality for AR is needed to provide symptom relief, regulate immune system function, decrease frequency and severity of AR recurrence, and prevent the condition from progressing.

The results from our previous international, multicenter clinical study in collaboration with South Korea revealed that 4-week long, active acupuncture treatment was significantly better at reducing AR symptoms compared with sham acupuncture and non-active treatment [13]. Furthermore, AR symptoms continued to reduce in the subsequent 4-weeks of follow-up, indicating the residual effect of acupuncture. Previous studies have demonstrated that moxibustion has a regulative effect on immune system function [14, 15]. Consequently, we have optimized the intervention scheme to warm needling. There are two types of warm needling, the one we used consists of placing an ignited moxa stick on the handle of the needle after insertion. Our hypothesis is that warm needling will achieve equal or better long-term symptom relief of AR and reduce its recurrence.

In previous studies of immunotherapy and pharmacotherapy effects on AR, the placebo control group treatment provided over 50 % symptom relief [16]. In previous clinical studies of AR treated with acupuncture therapy, placebo acupuncture was widely adopted as the control group. In this study, however, we have selected western medicine as the positive control instead of placebo acupuncture. Oral antihistamines are usually the first-line medication for AR symptom relief. Loratadine, as a second-generation antihistamine agent, has a strong selective antagonistic effect on the peripheral histamine H1 receptors, providing long-lasting effect without sedating the central nervous system. Not only is loratadine used in relieving and preventing AR-associated symptoms such as rhinorrhea, itching, sneezing, nasal blockage, and ocular symptoms [17, 18], it is also widely used in the treatment of other allergic diseases. After a detailed evaluation of the desired and the adverse effects, we chose loratadine as the intervention for the control group.

We have designed a multicenter, randomized controlled trial (RCT) for patients with PAR, using oral loratadine as control. The purpose of this trial is to answer two questions: (1) is the effect obtained by warm needling equal to or better than that achieved by loratadine? and (2) is the treatment of warm needling safe for patients with PAR?

The study was registered on ClinicalTrials.gov (NCT02339714).

## Methods

### Study design

The trial is designed as multicenter, parallel-group, randomized, single-blinded (outcome assessors), non-inferiority trial, comparing the differences between warm needling therapy and loratadine for PAR.

We will recruit 98 patients with PAR from three hospitals in China. According to their group assignment, patients will receive either 12 sessions of warm needling or the oral medication loratadine for 4 weeks.

The study design flowchart is presented in Fig. 1, and the study design schedule is shown in Table 1.

**Fig. 1 Fig1:**
[figure not shown]
Flowchart of the study design

**Table 1 Tab1:** Study design schedule

Period	Screening	Baseline	Treatment (W1–4)		Follow-up (W5 − M6)	
Time	W − 1	W0	W2	W4	M3	M6
Eligibility	X					
Demography and medical history	X					
Physical examination	X					
Informed consent	X					
TNSS	X	X	X	X	X	X
TNNSS	X	X	X	X	X	X
RQLQ	X	X	X	X	X	X
Adverse event			X	X		
Compliance			X	X	X	X

*RQLQ* Rhinoconjunctivitis Quality of Life Questionnaire, *TNSS* Total Nasal Symptom Score, *TNNSS* Total Non-nasal Symptom Score

### Study population

#### Trial location

We will recruit patients from three hospitals:Guang’an Men Hospital of China Academy of Chinese Medical Sciences (CACMS)Acupuncture and Moxibustion Hospital of CACMSMentougou Hospital of Traditional Chinese Medicine (TCM).

The three research centers are all situated in the capital of China.

#### Inclusion criteria

Participants will be eligible if they meet all of the following criteria: (1) are aged 18–60 years, (2) meet the classification criteria of moderate to severe PAR according to the Allergic Rhinitis and its Impact on Asthma (ARIA) guidelines, (3) exhibit at least one positive result on the allergy skin prick reaction test, (4) a 7-day mean Total Nasal Symptom Score (TNSS) ≥4 before treatment, and (5) agree to participate in the study willingly and voluntarily and sign the informed consent.

#### Exclusion criteria

Patients will be excluded if they have any of the following conditions: (1) suffer from other diseases that have an influence on PAR symptoms, (2) a moxa smoke allergy, or a severe needle phobia, (3) have experienced an acute paranasal sinusitis or respiratory tract infection within the previous 2 weeks, (4) a history of chronic paranasal sinusitis or chronic nasal sinusitis as shown by paranasal sinus computed tomography examination, or history of organic nasal cavity disease or nasal cavity surgery, (5) radiographic signs of pulmonary inflammation, (6) paroxysmal respiratory diseases such as asthma, (7) have taken antihistamines (including H1 and H2 receptor blockers), glucocorticoids, decongestants, mast cell membrane stabilizers, leukotriene antagonists, antibiotics or other prohibited drugs (including nasal, oral, or ophthalmic usage) or herbal preparations for AR within the last 2 weeks, (8) have undergone specific immunotherapy or systematic hormone therapy within the year prior to enrollment, (9) have received acupuncture and moxibustion, nasal inhalation of herbal medicine, physical therapy or other external treatment for AR within the last 2 weeks, (10) suffer from a mental disorder, malignant tumor, severe cardiovascular disease, severe endocrine disorder, tuberculosis, hepatitis, or serum creatinine or aspartate transaminase/alanine transaminase (AST/ALT) above twice the normal level, and (11) be unable to cooperate in the trial.

### Study procedures

#### Recruitment

In order to achieve the target enrollments of participants, clinical recruitment flyers were placed in three hospitals. Clinical recruitment staff will be in charge of the enrollment process of the 98 participants with PAR. Participants will be screened based on the inclusive and exclusive criteria, be briefed on the purpose, procedures, treatments and possible risks of the trial, and be clearly inform of their rights to discontinue participation in the clinical study. The screening process takes about 1 week, requiring the participants to fill in questionnaires on symptoms during the 1-week period. Upon participants signing off the consent forms, the staff will then assign the recruited patients to different intervention groups.

#### Randomization

The patients will be randomly assigned in a 1:1 ratio to the warm needling group or the loratadine group. The randomization sequence was computer-generated by the Clinical Evaluation Center of CACMS and the corresponding group name will be kept in a sealed and consecutively numbered security envelope. The envelope will be kept by the recruitment staff of the three centers. After all patients have signed the informed consent form, the envelopes will be opened. The patients will receive either warm needling treatment or oral medication of loratadine treatment according to their assigned group.

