## Discussion

The results of this study are expected to provide reliable evidence for the long-term efficacy of warm needling in the treatment of PAR.

This trial is designed as a non-inferiority trial. In our previous study comparing acupuncture and sham-acupuncture (placebo), the effectiveness of acupuncture has been proven. Therefore, we chose loratadine as the control group intervention in this trial so as to compare the differences between them, whether warm needling has an equal effect or is better than loratadine. Since western medicine is clearly being provided to the control group, with warm needling to the treatment group, it is difficult for us to achieve blinding of the participants and operators. Therefore, we chose blinding of the outcome assessors and the statistical analysts. To reduce the potential bias, strict random allocation concealment will be applied to minimize the differences between the two groups.

In winter, the cold climate, especially in the morning, is the commonest trigger of AR [32]. In TCM, AR is differentiated as a deficiency of *Wei Qi*, caused by external Wind and Cold; due to this pathogenesis of AR, warm needling at *Dazhui* (GV14) was included in the treatment. Moxibustion plays an important role in the prevention and treatment of disease [33], and previous research has reported that moxibustion has a positive effect on RA [34]. [name], the distinguished veteran doctor of TCM, has established the therapeutic method as strengthening *yang* and expelling Cold for AR. In the treatment, warm needling was applied at *Dazhui* (GV14), combining with acupuncture at local acupoints. *Dazhui* (GV14) is the confluent acupoint of the three *yang* meridians of hand and foot and the Governor Vessel. Hence, this point is also named as “*yang* within *yang*.” Moxibustion at *Dazhui* (GV14) acts by invigorating *yang qi* of all the *yang* meridians, promoting the circulation in the Governor Vessel, expelling Cold and consolidating the defensive *qi*. Therefore, this acupoint is especially suitable for the treatment of allergic rhinitis, asthma, common cold, and the other disorders caused by *yang* deficiency [35].

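### Recruitment staff hold the allocation envelopes and opening is tied only to consent, which weakens the strict concealment the trial relies on and does not exclude allocation before baseline TNSS

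*Protocol article*

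**What the plan says.** All references are to the protocol article.

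- **Enrolment.** The Recruitment section states: "Clinical recruitment staff will be in charge of the enrollment process of the 98 participants with PAR".
- **Assignment.** The same section ends: "Upon participants signing off the consent forms, the staff will then assign the recruited patients to different intervention groups".
- **Sequence.** The Randomization section states: "The randomization sequence was computer-generated by the Clinical Evaluation Center of CACMS". It adds that "the corresponding group name will be kept in a sealed and consecutively numbered security envelope".
- **Custody.** The next sentence is: "The envelope will be kept by the recruitment staff of the three centers".
- **Opening.** The section continues: "After all patients have signed the informed consent form, the envelopes will be opened". It does not say who opens the envelopes.
- **Blinding.** The Blinding section says operators and patients cannot be blinded. The outcome evaluator and the statistical analyst are.
- **Reliance on concealment.** The Discussion concedes the lack of participant and operator blinding and answers that, to reduce bias, "strict random allocation concealment will be applied to minimize the differences between the two groups".
- **Schedule.** Table 1 marks informed consent in the screening column (W-1) only, and TNSS at both W-1 and W0. It has no row for randomization.

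**The concern.** Concealment works when the person deciding whether and when a patient enters cannot know or influence the next assignment. Here the group that screens and enrols also stores the assignments. Several exclusion criteria need judgement, such as severe needle phobia, inability to cooperate, or another disease that affects symptoms. Those staff therefore have real discretion over who enters.

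Two things are at stake. The first is selection: if an assignment became known early, entry could be steered. The second is the baseline. The primary outcome is change in TNSS from baseline to 6 months after treatment, and eligibility needs a 7-day mean TNSS of at least 4. Patients fill in the symptom questionnaires during screening. A patient who already knew the assignment might report differently in the week that decides eligibility, or at W0, and the distortion would pass directly into the change score.

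**Working it through.** The point is procedural, so the check is to set the sections side by side. The protocol states no figure on this point, and its sample size does not bear on it.

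**Step 1: who does what.**

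| Task | Who | Section |
|---|---|---|
| Generate sequence | Clinical Evaluation Center | Randomization |
| Screen and enrol | Recruitment staff | Recruitment |
| Keep envelopes | Recruitment staff, three centers | Randomization |
| Assign patients | The staff; in context, recruitment staff | Recruitment |
| Open envelopes | Not named | Randomization |

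Generation is separated from recruitment. Custody is not, and assignment appears not to be. That recruiters personally open the envelopes is a likely inference, but it is not stated.

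**Step 2: when allocation happens.** Three accounts can be drawn from the document.

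1. *Table 1.* Consent is at W-1, before W0. If envelopes are opened on consent, allocation can be known during the screening week and before the W0 TNSS.
2. *Recruitment section, in the order written.* Screening, about one week of symptom questionnaires, consent, then assignment. Here the 7-day TNSS is known before assignment. But consent then comes after a week of study questionnaires, which does not match consent at the screening visit in Table 1.
3. *Randomization section, read literally.* Envelopes are opened once all patients have consented. That is opening in a batch, which does not fit assigning patients as they are recruited. The intended meaning is probably each patient in turn, but the text does not say so.

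**Step 3: is there any other gate?** The only stated condition for opening is signed consent. The inclusion criteria make the 7-day TNSS and consent joint conditions of eligibility. No sentence, however, requires confirmed eligibility or a recorded W0 TNSS before an envelope is opened. Account 1 is therefore not excluded, and nothing in the document establishes it either.

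**Step 4: do other features close the gap?**

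- *Assessor blinding* protects the evaluator's part of the measurement. It does not blind the patients, who report the symptoms.
- *Baseline adjustment* for center, severity and the baseline outcome value can absorb measured imbalance. It cannot reliably correct selection on unmeasured features, or an error in the baseline score itself.
- *Training and monitoring* (Monitoring section) cover envelope use and three-monthly external visits. They make misuse less likely and easier to detect, but do not move custody away from recruiters.

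**The case against.** The strongest reply is that sealed, consecutively numbered security envelopes are a recognised method of concealment. A center separate from the recruiters generates the sequence by computer, staff are trained in using the envelopes, and a team independent of the investigators and the sponsor monitors the three hospitals every 3 months. All of this stands. A reader might infer that concealment is defeated, or rests on trust alone. The documents do not support that: custody creates an opening for misuse, but it does not disclose the sequence.

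A reader might also infer that recruiters can predict the next assignment. No block size is given, so predictability cannot be argued from the text, and seeing an assignment early would mean breaching a sealed envelope.

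On timing, the reply is that Table 1 does not show when randomization occurs, that the Recruitment section suggests a late assignment, and that an article may leave the exact moment to the full protocol. This limits the claim. It is not established that allocation precedes baseline, only that the stated trigger permits it. The reply does not remove the conflict over when consent is taken, nor the literal batch wording. Those are inconsistencies in what is printed, not omitted detail. Custody by recruiters is likewise a stated choice.

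**Conclusion.** The point holds in a limited form. Recruiter custody, combined with enrolment and in context assignment, weakens the concealment that the Discussion calls strict, in a trial where patients and operators are unblinded. Allocation before the 7-day TNSS is confirmed and before the W0 TNSS is recorded is not excluded, and the three accounts of timing need to be reconciled.

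The size of any bias cannot be estimated. It would depend on how many entries were influenced and how far those patients differed in expected TNSS change, and the document gives neither. It may be tempting to choose values and compare the product with the stated delta of 0.2, but such inputs would be arbitrary, and the delta is given without a unit. No change in sample size follows.

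The verdict assumes that the staff who assign patients are the recruitment staff, as the context of the Recruitment section indicates. If a different person assigns, the custody point remains but is weaker. This is an inexpensive improvement that should be made; it is not a flaw that invalidates the design.

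**What to change.** 1. **Move custody and release.** Have the Clinical Evaluation Center, which already generates the sequence, hold it and release each allocation by telephone or message. If envelopes are kept, give them to an existing person at each site who takes no part in recruitment.
2. **Set the gate.** Release an allocation only after consent, confirmed eligibility including the 7-day TNSS, and the W0 TNSS have all been recorded for that patient.
3. **Reconcile the text.** Align Table 1 and the Recruitment and Randomization sections to one order: consent, screening week, baseline, allocation. Add a randomization row to Table 1 after the W0 measurements, state who opens or releases each allocation, and reword the opening sentence so that it refers to each patient individually.

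The cost is one call or message per patient, about 98 in total, and possibly a short wait for release. Central release also needs the Center to be reachable when patients enrol, which the document does not state; the site-based option avoids this. The Trial status section says recruitment is just beginning, so most or all patients could still be covered.

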#### Blinding

Since the acupuncture group and the medication group have different characteristics regarding intervening measures and approaches, it is not feasible to blind both the operators and patients. Instead we adopted the single-blinded trial where both the outcome evaluator and statistical analyst will be blinded to the groupings and they will not be involved in any part of the treatments during trial to ensure that there no form of bias results. At the end of the observation period, un-blinding is permissible only after database blinding approval and data block.

#### Follow-up

Upon completion of the 4-week treatment period, there is a further 6-month follow-up period. The research staff will continue to follow the participants via telephone communication and short messaging service (SMS). The frequency of follow-up is monthly and we will keep a record of the assessment of symptoms and medication compliance or changes. In the event of participants discontinuing or deviating from intervention protocols, the study staff will record the reasons for this and their medications and then exclude the participants from the study, and the latest outcome data including symptoms and frequency of the attacks.

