#### Concomitant care and intervention

During the treatment and follow-up period, the subjects are advised to avoid antigens. The participants are prohibited from taking medications such as oral and intranasal antihistamines, intranasal steroids, intranasal decongestant, antibiotics or oral leukotriene receptor antagonists. Only for patients with severe symptoms are intranasal steroids allowed to be used. The type of medicine, dosage and usage will be recorded in the diary card for analysis. For the other complicated chronic diseases, the patients must continue taking their routine medication and other therapies. The research staff will record the names of those diseases and the names of medications and therapies in the case report.

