#### Discontinuation of the intervention

The intervention is to be terminated in the cases of severe adverse events, withdrawal of participants by their own wish and unpermitted medication use.

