#### Primary outcome measure

The average change in the TNSS will be measured blindly by comparing the baseline score in each group with that at 6 months after treatment during the follow-up period. The TNSS is determined in terms of the severity of rhinorrhea, nasal itching, nasal obstruction, and sneezing.

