#### Statistical methods

The statistical analysis will be performed with SPSS 17.0 software (SPSS Inc., Chicago, IL, USA) in the Clinical Evaluation Center of CACMS. We will perform baseline adjusted analyses for the following variables (the center and severity), and the baseline value of the corresponding outcomes will be assessed. The data analyses will be conducted on an intention-to-treat population. Descriptive statistics will be used to compare the baseline measures and patients’ characteristics between the two groups. Regarding the primary and secondary outcome measures, the two-sample *t* test or Wilcoxon rank sum test will be used to compare the differences between the two groups from baseline to the end of treatment (*p* < .05 will be considered statistically significant). If an imbalance occurs in baseline characteristics between the two groups, ANCOVA will be applied.

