#### Missing data and sensitivity analysis

The data used in the main statistical analysis should be collected in the fourth week of the treatment and at the half-year follow-up. In order to avoid missing data, we will provide an economic compensation for participants who have finished the trial and provided the completed data. The investigators have a wealth of experience in managing patients and collecting data in previous trials. They record the contact information of participants and keep in touch with them through a variety of means during the treatment and follow-up periods.

If the data are not obtained, we will record the time and reason for the missing data and will analyze the assumed missing data mechanism. For these missing data, we will use the multiple imputation adjustment approach. After the main analysis, we will perform a sensitivity analysis for the various datasets to enable us to judge the impact of missing data on our results.

A fully specified statistical analysis plan will be written independently.

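### Participants who stop or deviate from treatment are excluded from the study, so their month-6 TNSS is not collected; this conflicts with the intention-to-treat analysis

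*Protocol article*

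**What the plan says.** All references are to the protocol article.

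- **Follow-up.** The trigger is "In the event of participants discontinuing or deviating from intervention protocols". The action is that "the study staff will record the reasons for this and their medications and then exclude the participants from the study". The sentence then ends "and the latest outcome data including symptoms and frequency of the attacks", a clause without a clear verb.
- **Discontinuation of the intervention.** The whole section is one rule: "The intervention is to be terminated in the cases of severe adverse events, withdrawal of participants by their own wish and unpermitted medication use". This ends the treatment; it does not mention follow-up.
- **Primary outcome measure.** The primary analysis rests on "comparing the baseline score in each group with that at 6 months after treatment during the follow-up period".
- **Statistical methods.** "The data analyses will be conducted on an intention-to-treat population".
- **Missing data and sensitivity analysis.** The time and reason for missing data are recorded and the assumed mechanism is examined. Then: "For these missing data, we will use the multiple imputation adjustment approach". A sensitivity analysis follows.
- **Concomitant care and intervention.** Listed medications are prohibited during treatment and follow-up, with one exception: "Only for patients with severe symptoms are intranasal steroids allowed to be used".

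No section says that an excluded participant is still assessed at month 3 or month 6.

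**The concern.** An intention-to-treat analysis of a month-6 outcome needs month-6 measurements on everyone randomised, as far as they can be obtained. The Follow-up section instead makes leaving treatment, or departing from it, a reason to leave the study. A participant who stops needling in week 2 would have no month-6 TNSS, although still willing to be assessed.

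This loss is unlikely to be random. The stated reasons for ending the intervention include adverse events, the participant's own wish and unpermitted medication, and each can reflect how treatment is going. The arms also differ in burden: 12 needling sessions with a possibility of burns or pain, against one daily tablet. Patients and operators know the allocation, and the article does not define what counts as deviating. Exclusion can therefore depend on arm and on symptoms. In a non-inferiority trial with a margin of 0.2, a modest selective loss can matter.

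An analysis plan written later cannot repair this, because the rule governs which data are collected.

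**Working it through.** **1. The sections side by side.** Discontinuation of the intervention ends treatment. Follow-up ends participation for the same people and for those who deviate. Statistical methods promises an intention-to-treat population, and the primary outcome is at month 6. The unclear last clause of the Follow-up sentence has two readings: the latest data are recorded before exclusion, or they are excluded as well. Under both, month-6 TNSS is absent for anyone excluded earlier.

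**2. The plan's own sample size.** Inputs from Sample size calculation: mean TNSS change 4.90 (SD 3.54) after acupuncture and 3.4 (SD 1.0) after loratadine, power 80%, alpha 0.05, delta 0.2, dropout 20%.
- Average SD = √((3.54² + 1.0²)/2) = 2.601. Distance from the margin = (4.90 − 3.4) + 0.2 = 1.7.
- Normal formula, one-sided 0.025: n = 2 × 2.601² × (1.960 + 0.842)² / 1.7² = 36.8, so 37 per group. The unequal-variance t version gives 39, the stated figure.
- 39/(1 − 0.20) = 48.75, so 49 per group, as stated.

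The sample size reproduces, and this point does not change it.

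**3. Shift in an analysis of those who stay.** Let a share q of an arm be excluded, with a true month-6 improvement g points below that of those kept. The arm's true mean is the mean of those kept minus q × g, so the kept overstate it by q × g. With the same g in both arms:

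shift = (q₁ − q₂) × g

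The document gives neither q nor g, so these values are assumptions:

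| Difference in exclusion | Deficit g (points) | Shift (points) |
|---|---|---|
| 0.05 | 1 | 0.05 |
| 0.10 | 2 | 0.20 |
| 0.15 | 3 | 0.45 |

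The middle row corresponds, for example, to 20% against 10% excluded, about 10 against 5 of 49. If the deficits differ between arms, the shift is q₁g₁ − q₂g₂, so equal exclusion rates do not guarantee zero bias.

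**4. Scale.** With 39 per group, SE = 2.601 × √(2/39) = 0.589, so a shift of 0.20 is 0.20/0.589 = 0.34 SE. If it favours warm needling, the false non-inferiority rate at the margin (one-sided 0.025) becomes 1 − Φ(1.960 − 0.340) = 5.3% instead of 2.5%. A shift of 0.10 gives 3.7%. If the shift goes the other way, the cost is power.

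**5. Effect of imputation.** Under the planned multiple imputation, g is replaced by the deficit that remains after conditioning on the observed scores. If earlier scores explained half of a 2-point deficit (an assumption), the middle row would fall to 0.10 × 1 = 0.10. Someone excluded in week 2 offers little beyond baseline to condition on.

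**The case against.** The strongest defence is that Follow-up concerns conduct while Statistical methods defines the analysis set. Nothing says that excluded participants leave the analysis. The plan records reasons for missing data, examines the mechanism, imputes and runs a sensitivity analysis. That stands as far as it goes: a reader might infer that intention-to-treat is abandoned at the analysis, and the document does not show this. It does not answer the loss of data that could have been collected. Imputation models those values largely from participants who stayed, and a sensitivity analysis shows fragility without supplying outcomes.

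Three further inferences are tempting and go beyond the text:
- **That only the latest data are kept.** The clause is too unclear to establish this.
- **That prohibited medication during follow-up is a stated trigger for exclusion.** The trigger refers to intervention protocols, and the interventions last 4 weeks. The prohibition through follow-up and the compliance checks at months 3 and 6 (Table 1) make this a possible reading, no more. Because intranasal steroids are permitted for severe symptoms, not every participant who relapses and treats the relapse would be deviating.
- **That 0.20 points is the bias of the planned analysis.** It is the bias of an analysis of those who stay. Imputation shrinks it to the extent that earlier scores predict month 6.

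It is also fair to say that 0.20 equals the whole margin mainly because the margin is small, and that the shift is about a third of a standard error.

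**Conclusion.** The point holds. As written, the Follow-up section conflicts with the intention-to-treat population and the month-6 primary outcome, and it creates avoidable missing primary data for reasons that can depend on treatment and symptoms. That conclusion rests on the text alone and needs no assumed rate.

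The size is illustrative: 0.20 points, range 0.05 to 0.45, before any correction by imputation. It assumes exclusion differences of 5 to 15 percentage points, deficits of 1 to 3 points that are equal in both arms, and a margin of 0.2 in TNSS points. The direction is uncertain because exclusions may occur in both arms. The point should be settled before the trial proceeds far, since month-6 assessments that are not made cannot be recovered. The article describes recruitment as just beginning.

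**What to change.** Reconcile Follow-up, Discontinuation of the intervention, Statistical methods, and Missing data and sensitivity analysis by separating the end of treatment from the end of study participation. In Follow-up, replace the exclusion instruction with text to this effect:

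*Participants who stop or deviate from the intervention stay in follow-up unless they withdraw consent. TNSS, TNNSS and RQLQ are still collected at every scheduled time to month 6 by the blinded outcome evaluators, with medication use recorded. These participants are analysed in the group to which they were randomised.*

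Reserve multiple imputation for data that are truly missing. Rewrite the unclear last clause of the Follow-up sentence so that data already collected are plainly retained.

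The cost is small: a few more participants are assessed at the existing month-3 and month-6 time points. The monthly telephone and SMS contacts by research staff can help to keep them in touch, but scoring should stay with the blinded evaluators. The compensation for finishing the trial needs aligning so that it covers participants who stopped treatment but completed follow-up. The planned 49 per group is unchanged, and no dose, medication rule or rule for stopping treatment is altered. If all 49 per group gave month-6 data, power on the plan's own assumptions would be about 89 to 90%, against about 81 to 82% with 39.
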